also show effectiveness when delivered via eHealth.25 Specifically after LLA, education and skill development can support the recovery process, especially for older adults.27 However, to date, based on our review of the published evidence, there are only five publications28-32 using telehealth with people after LLA, and only one face-to-face study33 which tested effectiveness of self-management interventions after LLA. That is, we could not identify any published eHealth interventions using self-management for adults with LLA. Given the number of Canadians with a LLA each year, the declining emphasis on inpatient rehab, it is imperative to work with key stakeholders to develop an test acceptable and feasible rehab options. eHealth solutions post LLA have the potential to increase access and improve health outcomes,27, 33 but we need Canadian data before this delivery mode can be integrated into clinical practice. We completed foundation work with stakeholders (e.g., adults with LLA, clinicians, community organizations, etc.) to develop and test feasibility for an eHealth intervention34-36 called **S**elf-**M**anagement for **A**mputees using **R**ehabilitation **T**echnology (SMART) that is ready to test effectiveness, and describe key implementation factors for future integration into clinical practice, if appropriate.

**1.2. Principal research questions:** We will use a Type 1 Effectiveness-Implementation Hybrid Design2 randomized controlled trial (RCT) to evaluate the 6-week effectiveness (and 4-week retention effect) of SMART on patient-relevant outcomes, while documenting implementation factors. Please note, we chose the primary (and secondary) outcomes based on feedback from adults with LLA who identified walking (e.g., mobility) and new identity as of great importance in the recovery process. Our research questions are:

**Q1.** What is the effect of SMART on walking confidence and capacity in adults aged over 50 years with a LLA?

**Q2.** What is the effect of SMART on physical activity identity, knowledge, self-efficacy, and falls confidence in adults aged over 50 years with a LLA?

**Q3.** What are the essential factors required to implement SMART into clinical practice?

We hypothesize that older adults with LLA who receive usual care and the SMART intervention, compared with usual care, paper-based education, and social visits (control group intervention) will have greater positive change in:

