**H1.** walking capacity, operationalized as higher change score with the two-minute walk test;37

**H2.** physical activity identity, knowledge, self-efficacy, and falls confidence, operationalized as higher change score with the physical activity identity questionnaire,38 patient activation measure,39 and activities specific balance confidence scale.40

**Work completed to support this proposal:**We have completed a number of key feasibility and development studies to support this next phase of testing effectiveness of the innovation (SMART eHealth intervention) and describing its implementation. Using a participatory action research approach,1 we created a Steering Group with our clinical co-investigators (Co-applicants (Co-A) clinicians **[name], [name], [name] and [name]** and patient partners **[name], [name], [name])**. We met 8 times over two years. We co-created the SMART web-based app (please see **Appendix A**), designed to guide adults with LLA to actively engage in self-management. The app is asynchronously monitored through a website portal. There were 31 clinicians, and 26 adults with LLA (73% men) who engaged in semi-structured interviews to identify common themes in the recovery process, and app content to best augment existing LLA rehab. Key findings were: adults with LLA (i) requested tools and strategies to return to walking and independence in activities of daily living (ADLs); and (ii) perceived a new identity after amputation. This feedback was incorporated into the SMART intervention, for required content and the need for peer support to enact the principles of self-management.34, 36 In parallel, we conducted a systematic review and meta-analysis of telehealth interventions for patients with lower limb musculoskeletal surgery41 to identify effective behavior change techniques (BCTs)42, 43 to incorporate into SMART. Self-efficacy44 and action planning theory45 informed the development of SMART. We were also guided by the Theoretical Domains Framework46, 47 to incorporate relevant BCTs within SMART. For example, social support, instruction on how to perform the behavior, self-monitoring behavior, etc. We currently completing a pilot study with a mixed method approach to address design and SMART intervention fidelity with 10 participants who have lived with a LLA for at least 1 year.48

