**2.4 Protecting against bias - Blinding:**Blinding of participants for the RCTs on the effect of eHealth interventions is impossible because of nature of intervetnions.66 Therefore, it is difficult to blind participants to the intervention received. The assessors will be blinded to group allocation, we will complete the primary outcome (TUG and ASCQ) first, and participants will be asked not to disclose their group allocation during assessments.66 Furthermore, we will have separate trainers for each group (to minimize trainer bias); and the primary outcome measure, the TUG is a performance-based measure with standardized instructions. Finally, all statistical analyses will be conducted by a blinded statistician.

**2.5 Inclusion and Exclusion Criteria:**To be included, participants will: have a unilateral dysvascular- or diabetic- related LLA (transtibial or transfemoral);3have conducted the casting for their initial prosthetic limb (up to 2 years); be aged ≥ 50 years (85% of adults with LLA);3 have a computer or tablet and have access to the internet, and self-identify as being able to speak and read English. We will exclude adults with substantial health conditions (e.g., congestive heart failure, diagnosed dementia); those anticipating further surgery (e.g. LLA revision) as identified by our study sites’ physiatrists; and an ability to use a tablet (e.g./ using hands for typing). Given these criteria, the results of this study will not be generalizable to all adults with LLA such as the very young and those who do not speak English. As most people with LLA are >50 years old and more than 90% of the population of BC and ON speak English, we are confident of obtaining a representative sample.

**2.6 Duration of Intervention:**Participants in the SMART group will receive the intervention for six weeks. Participants in the control group will be contacted weekly for a similar 6 week period.

**2.7** **Frequency and Duration of Follow-up:**There are six weekly SMART modules with each taking approximately 20 to 30 minutes to complete. Individuals will be encouraged to complete one module a week to reduce any perceived burden, and gradually integrate the information. Participants from both groups will receive a weekly contact: SMART group participants will receive a 20 minute telephone call/Zoom video call from peers, and the Control group participants one email or phone call by trainer.

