**2.8 Outcome Measures:**

Note: all measures that involve participants walking will be conducted under remote supervision via Zoom.

***Primary Outcome:*** In contrast to medical interventions, many eHealth interventions have no pre-eminent outcome (e.g., reduced hypertension).66 Our primary outcome was selected to address the goals of the self-management program (patient perceived problems22, 67) identified in our previous work which is walking. We operationalized this as the Timed Up and Go Test (TUG), a performance measure of walking capacity -- deemed the strongest determinant of health-related quality of life and prosthetic walking proficiency in adults with LLA.68 It is widely used in intervention studies of the LLA population,69 with strong evidence of reliability, validity, and responsiveness.37, 70 The ability to walk longer distance permits people to explore and engage with their environment, which directly influences their choice of activities and social participation.71 Poor walking capacity may eventually lead to prosthetic abandonment.72 The Timed Up and Go (TUG) is a functional assessment that assesses aspects of mobility including the sit to stand transitions, gait initiation, acceleration and deceleration, and turning (Clemens et al., 2018). The TUG has been shown to be both a reliable and valid measure to evaluate how individuals with lower limb amputation function within their environment (Clemens et al., 2018). A mobile version of the TUG has also been shown to have excellent validity and reliability in the amputee population, making it an ideal tool for a mobile platform (Clemens et al., 2018). Participants will be asked to use a 48-cm-high armchair and mark a spot 3 meters from the front legs of the chair (Clemens et al., 2018). Participants would then be timed, starting from a sitting position, then standing and walking 3 meters, turning around and walking back and sitting back in the chair Clemens et al., 2018).

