**Ambulatory Self-Confidence Questionnaire (ASCQ).** Perceived self-efficacy (confidence) includes the concept that one can exercise control over their health-related outcomes and activities and can therefore be an indicator in individuals perceived confidence in ambulation (Bandura, 2004). The ASCQ is a 22-item questionnaire where participants are asked to rate questions on a scale from 0 (not confident at all) to 10(extremely confident). (Asano et al., 2007). The ASCQ has been shown to have both reliability and validity in community-dwelling older adults (Asano et al., 2007).

**Timed Up and Go (TUG) Test.** The TUG assesses an individual’s ability to stand from a sitting position, walk three meters, turn around, walk back and sit back in the chair.87 It captures aspects of mobility capacity (what an individual can do)86 including sit-to-stand transitions, gait initiation, acceleration and deceleration, and turning.87

***Secondary outcomes*** are aligned with the performance objective of SMART and adults with LLA challenges (mentioned in section 1.2.) as well as patient-reported outcomes to capture patients’ views of their symptoms, and their functional status,61, 73 including:

- Physical Activity Identity (PAI) scale is a 9-item measure of an individual's identification with exercise as an integral part of the concept of self,38 with high test-retest reliability and good validity. We will use a modified version of the PAI questioning the extent that physical activity is considered a part of an individual’s aspect of self.74
- Activities Specific Balance Confidence Scale (ABC) isa 16-item self-reported measure of balance self-efficacy during ambulatory activities with total score of 0 to 100.40
- Euro Quality of Life – Five Level Instrument (EQ-5D-5L) assesses five dimensions of health-related quality of life: mobility, self-care, usual activities, pain/discomfort, and anxiety/depression.88
- Tenacious goal pursuit (TGP) assesses the tendency to persist and increase effort in pursuing goals facing obstacles.89
- Action planning scale (AP) assesses whether people had formed a plan which links goal-directed behavior to environmental cues by identifying when, where, and how to act.90 We will assess the AP for “exercising”, “skin monitoring”, and “cleaning the prosthesis”.

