**2.10 Sample Size:**Our sample size calculation is based on identifying SMART is more effective than standard care from a clinical point of view (Clinical Superiority design),75 and minimize any potential waste of resources.76 We are planning to compare the 2-MWT using a ratio 1:1. In a previous study, the mean (SD) of clinically important change in distance walked in 2 minutes at discharge from the rehab facility was 13.6 (19.9) m in adults with unilateral LLA (mean age = 66 y).37 Assuming minimum important difference of 13.6 m, we will need to enroll a minimum 34 participants per group to be enable to reject a null hypothesis of no difference in means of walking capacity between the 2 groups with 80% power. The type-I error probability associated with this 2-sided test of the null hypothesis is 0.05. Our sample size is based on the feasibility of recruiting 2 adults aged over 50 years with an LLA, per site within 18 months, and with 68 participants at final assessment (accounting for participant attrition) we can have enough power to detect a difference in the primary outcome, i.e., 2-MWT. Acknowledging the challenges with participants,77 20% attrition rate, and non-compliance rate in RCTs, we will recruit 82 participants (41 per arm including both men and women).The target sample size will also facilitate estimates for adherence, and the number of participants with certain covariates (e.g., sex, gender), and inform the sample size calculation and stratification for the implementation study.

**2.11 Health services research issues:** Cost and cost-effectiveness of eHealth interventions have been demonstrated for patients with chronic disease conditions.78 However, we will not do a formal cost analysis in this study.

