**Figure 2: Study Timeline**

**2.16 Data Analyses:**The assumptions for parametric analyses will be evaluated. Normal distribution will be evaluated using the one-sample Kolmogorov-Smirnov test. Qualitative comparison of variable balance will be made, including determination of prognostic importance. Descriptive statistics of training time and number of training sessions for the treatment group (collected via tablet usage data) will be used to evaluate dose-response and adherence.

***Clinical Outcomes:*** Analyses will be conducted on a per-protocol basis (i.e., participants who completed the study) and then on an intention-to-treat basis for comparison (i.e., using multiple imputation).79 All primary and secondary outcomes will be compared between the intervention and control groups, using analysis of covariance (ANCOVA), controlling for baseline score and inpatient and outpatient units. To explore the findings, ANCOVA will be used to compare secondary clinical outcomes between groups. Endpoint and change score analysis of variance (ANOVA) tests will also be conducted to compare precision with ANCOVA for sensitivity analyses. To glean a better understanding, we will disaggregate the data by sex/gender and *key outcomes* (e.g., walking capacity and physical activity identity) and explore differences in our study.

***Study and intervention fidelity, and participant experience:***All audio-recordings of the qualitative interviews at T3 will be transcribed verbatim. Thematic data analyses80 will be used to identify key themes in the qualitative interviews. Three methods will be used to promote trustworthiness. Field notes will be used as a self-reflexive tool and member checking, (i.e., key participants will be invited to review the findings to determine how well they resonate with them). Multiple investigators will be involved in data coding as a form of triangulation. Interview results will complement the quantitative results to provide a more in-depth assessment of benefits and user acceptability.59

**2.17 Frequency of analyses:**An interim data analyses will be performed on the primary outcome when 50% of participants have completed T2. An independent blinded statistician will conduct the analyses and report findings to the Data and Safety Monitoring Committee (see *section 3.3*). If the results indicate the SMART or control arm is superior and sufficient information is available, we will terminate the trial to reduce subject burden.

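### The protocol names its primary outcome in conflicting ways (TUG and ASCQ, TUG alone, 2-MWT) and gives no rule for success; if either TUG or ASCQ could win at 0.05, the false-positive rate would be up to 9.75%

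*Protocol*

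**What the plan says.** The protocol identifies its primary outcome in several places, and they do not agree.

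- **Section 1.2, Q1** asks about two constructs: "What is the effect of SMART on walking confidence and capacity in adults aged over 50 years with a LLA".
- **Section 1.2, H1** uses one measure, which is neither TUG nor ASCQ: "walking capacity, operationalized as higher change score with the two-minute walk test".
- **Section 2.4** has both: "we will complete the primary outcome (TUG and ASCQ) first". The next sentence has one: "the primary outcome measure, the TUG is a performance-based measure with standardized instructions".
- **Section 2.8**, under the primary outcome, has one: "We operationalized this as the Timed Up and Go Test (TUG), a performance measure of walking capacity". The ASCQ follows in its own paragraph ("The ASCQ is a 22-item questionnaire where participants are asked to rate questions on a scale from 0"), before the secondary outcomes begin. It does not appear in the secondary list.
- **Section 2.10** bases the sample size on a third measure, with enough power to "detect a difference in the primary outcome, i.e., 2-MWT".

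On analysis, section 2.16 states "All primary and secondary outcomes will be compared between the intervention and control groups", by ANCOVA. It does not say whether success needs one or both of TUG and ASCQ, and it sets no order and no division of alpha. The only significance level in the protocol, two-sided 0.05, is in section 2.10 and belongs to the 2-MWT calculation.

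**The concern.** The ASCQ is either co-primary (2.4, first mention, supported by Q1) or has no rank at all (2.8). An analysis plan written later could adopt either reading and still claim to follow the protocol. The choice could then be made, or appear to have been made, with results in view.

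The two measures differ in their exposure to bias. Section 2.4 offers the TUG's performance-based, standardised nature as a protection, alongside blinded assessors. The ASCQ is a self-rating of confidence by participants who, the same section says, cannot be blinded, so neither protection reaches it fully. Under the present text, a trial with no effect on the TUG and a favourable ASCQ could be reported as positive on a primary outcome. If that route to success is open, the overall error rate for the primary claim also exceeds the level used for each test.

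**Working it through.** **1. The plan's own figure, and what it covers.** Inputs from section 2.10: difference 13.6 m, SD 19.9 m, two-sided alpha 0.05, power 80%, ratio 1:1.

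n per group = 2 × (1.960 + 0.842)² × (19.9 / 13.6)² = 33.6, rounded up to 34.

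This matches the stated 34 per group. It also shows that the 0.05 is attached to the 2-MWT. The protocol gives no effect, SD or alpha for TUG or ASCQ, so neither a sample size nor a power can be derived for them.

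**2. Readings that the text allows for TUG and ASCQ.** Assume each is tested at two-sided 0.05 at the final analysis.

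| Reading | Support in the protocol | False-positive rate for the primary claim |
|---|---|---|
| TUG alone is primary | 2.8; second mention in 2.4 | 5% |
| Both must succeed | Q1 joins confidence and capacity | at most 5%; the cost falls on power |
| Either suffices | first mention in 2.4; nothing excludes it | see step 3 |

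**3. The either-suffices case.** With independent test statistics:

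1 − (1 − 0.05)² = 1 − 0.9025 = 0.0975.

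With correlation ρ between the two statistics, and Z₁, Z₂ bivariate standard normal:

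rate = 1 − P(|Z₁| < 1.96 and |Z₂| < 1.96).

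The protocol gives no ρ, so a range is shown:

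| ρ (absolute value) | Rate |
|---|---|
| 0 | 9.75% |
| 0.3 | 9.5% |
| 0.5 | 9.1% |
| 0.7 | 8.3% |
| 0.8 | 7.8% |
| 0.9 | 7.0% |

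Both measures concern walking, so some correlation is plausible and 9.75% is an upper bound.

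**4. Fixed order (TUG, then ASCQ only if the TUG is significant).** If SMART has no effect on the TUG, any false claim requires a significant TUG first, which has probability at most 5%. If it does affect the TUG, the only possible false claim is on the ASCQ, tested at 5%. The rate for the pair is therefore at most 5% at the final analysis, whatever the correlation.

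**The case against.** A reader might infer that each outcome is tested at 0.05 and that the error rate therefore nearly doubles. The documents do not support that as a flat statement. The 0.05 is given only for the 2-MWT sample size, no either-one-wins rule is written, and 9.75% is the zero-correlation extreme. Two of the three readings in the table leave the rate at or below 5%.

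An order of testing or a division of alpha may also be set out in an analysis plan that is not shown, so its absence alone would not be a fault of the protocol. That is fair. It does not cure the naming: the protocol contradicts itself on which outcome is primary, and that is for the protocol to settle.

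Three further extensions are tempting and should be left aside.

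- The power cost of splitting alpha cannot be stated for TUG or ASCQ, because the only effect and SD available are those of the 2-MWT.
- The interim look in section 2.17 has no stated threshold. That is a separate problem and adds nothing to the size of this one.
- Module 1 lists rating confidence among its self-regulatory skills (section 2.2), but the protocol does not tie it to ambulatory confidence or to ASCQ answers. The bias concern rests on unblinded self-report alone.

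Finally, a single primary with an ordered second test is not the only valid choice. Given Q1, requiring both outcomes or splitting alpha would also be legitimate. What is required is that one rule be chosen and written down.

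**Conclusion.** The point stands as an inconsistency in the primary endpoint, with a conditional consequence for error control. The contradiction itself needs no assumption: it lies in the wording of sections 1.2, 2.4, 2.8 and 2.10.

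The inflation, from 5% to between 7.0% and 9.75% over correlations of 0.9 down to 0, rests on two assumptions that the protocol neither states nor excludes: two-sided 0.05 for each of TUG and ASCQ, and success on either. It applies to the final analysis only.

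The practical risk is that an unblinded self-report carries the primary claim after a null performance test. The matter should be settled before any outcome data are seen by group.

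**What to change.** In sections 2.4 and 2.8, state that:

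- TUG at T2 is the single primary outcome, tested at two-sided 0.05;
- ASCQ at T2 is the first key secondary outcome, tested at two-sided 0.05 only if the TUG result is significant, and reported with the caveat that participants were not blinded.

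This agrees with how 2.8 already operationalises the primary.

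In the same edit, reconcile H1 and section 2.10, which still name the 2-MWT; otherwise the protocol would keep a different primary in its hypothesis and its sample size. H1 also needs its direction checked, since the TUG is a time and improvement is a fall, not a higher score. Section 2.10 needs a justification on the TUG scale, because the 34 per group rests on 2-MWT figures and cannot simply be carried across.

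**Cost.** Ranking the outcomes is a change of wording and needs no extra participants for multiplicity. The sponsor gives up the option of claiming success on the ASCQ alone. Section 2.10 additionally needs a TUG effect and SD, which the protocol does not now contain.

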# 2. the proposed trial

**2.1 Study Design:**This is a Type 1 Effectiveness-Implementation Hybrid Design2 1:1 parallel single (assessor)-blinded randomized controlled trial (RCT) conducted online with participants from four Canadian sites (B.C.; London, ON; and two in Toronto, ON) to evaluate the 6-week effectiveness (and the 4-week retention effect) of SMART on patient-relevant outcomes, while documenting implementation factors.59Following the [RE-AIM](http://www.re-aim.org/) framework, a planning tool for implementation evaluation,60 we will assess the implementation of SMART. Also, a small end-of-trial qualitative study will be used to understand participants’ experience.61

**2.2 Trial Interventions:** Participants allocated to the intervention group will receive usual care after the LLA and access to **SMART**. We provide a detailed description of SMART using the TIDieR (Template for Intervention description and Replication) checklist62 provided in **Appendix B**. In **Appendix C** we provide a list of BCTs adopted for each module according to our systematic review and meta-analysis.41 Participants will access the SMART platform using their own computer/tablet, and will be screened for having a computer/tablet before enrolling in the study. In rare cases where a participant in B.C. does have a tablet, they may receive a tablet (Apple’s iPad) preloaded with a dedicated icon to enable direct connection with the SMART platform, if needed. Tablets will not be able to be provided to participants in Ontario.

**Content:** SMART is web-based eHealth intervention that has six educational and skill development modules. SMART is accessible through this link: <https://360.articulate.com/review/content/1afbca12-f6bb-465e-b40f-1029a6fa981b/review>

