| Who provided | The trainer will spend less than 2 hours to provide instruction for a participant to learn how to use the SMART, at baseline (T1). The SMART platform will be asynchronously monitored through a web portal by the trainer, who will observe participant progress and provide feedback if required. If there is no online activity within a 7-day (consecutive) period, the trainer will contact the participant to inquire the reasons for inactivity and troubleshoot any problems including technical issues.  Two peers will be identified by our clinician partners at each study site. Peers are mentors with LLA who support the individuals with LLA.65 The assessor will be a trained research assistant who will be blinded to participants assigned groups. The assessor will evaluate all participants at baseline (T1), end of the intervention (6-weeks) (T2), and 4-week retention period (T3). |
| How (modes of delivery) | SMART is an online, educational and training platform for individuals with LLA that is asynchronously monitored by a trainer through a website. SMART will be delivered via computer or tablet with support of peers. |
| Where | Participants will use one module of SMART per week. All participants will be evaluated by an assessor online via Zoom (a secure, UBC-based platform) at T1, T2, and T3. |

**Appendix C:** Behavioural change techniques used for contents of modules in Self-Management for Amputee Rehabilitation Using Technology (SMART)

| **BCTs** | **Self-regulatory skills** | **Mental wellness** | **Physical health** | **Residual limb management** | **Managing a prosthesis** | **Managing daily living activities** |
| --- | --- | --- | --- | --- | --- | --- |
| Goal setting (behaviour) | * | * | * | * | * | * |
| Problem solving |  | * | * | * | * | * |
| Action planning |  | * | * | * | * | * |
| Self-monitoring of behaviour |  |  | * | * | * | * |
| Social support (practical) | * | * | * | * | * | * |
| Social support (emotional) |  | * | * | * | * | * |
| Instruction on how to perform a behaviour | * | * | * | * | * | * |
| Information about antecedents |  | * | * | * | * | * |
| Information about health consequences |  | * | * | * |  |  |
| Demonstration of the behaviour |  |  | * | * | * | * |

**Appendix D.** Brief Action Planning (BAP) Flowchart

Developed by Steven Cole, Damara Gutnick, Connie Davis, Kathy Reims

Accessed from: <https://centrecmi.ca/wp-content/uploads/2018/11/BAP_flow_Chart_2016-08-08.pdf>

[figure not shown]

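### Section 2.5 excludes people who can use a tablet, the reverse of what is meant, and the B.C. tablet sentence in section 2.2 leaves device eligibility unclear

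*Protocol*

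**What the plan says.** Section 2.5 gives the inclusion criteria and then the exclusions. Among the inclusion criteria, a participant must "have a computer or tablet and have access to the internet". The exclusion list opens with "We will exclude adults with substantial health conditions (e.g., congestive heart failure, diagnosed dementia", goes on to people expecting further surgery, and closes with "and an ability to use a tablet (e.g./ using hands for typing".

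Section 2.2 sets the device rules in three consecutive sentences:
- The general rule: "Participants will access the SMART platform using their own computer/tablet, and will be screened for having a computer/tablet before enrolling in the study".
- For British Columbia: "In rare cases where a participant in B.C. does have a tablet, they may receive a tablet", the device being preloaded for access to the platform.
- For Ontario: "Tablets will not be able to be provided to participants in Ontario".

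Appendix B (the TIDieR checklist) describes the mode of delivery: "SMART will be delivered via computer or tablet with support of peers".

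**The concern.** The exclusion criterion has the wrong polarity. The verb governing the list is one of exclusion, and the item names an ability. This is operative text: screening forms, eligibility checks and the classification of protocol deviations are normally built from it. The rule as worded turns away the people the trial is for and passes those it means to keep out.

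The device rules raise a second, smaller problem. The B.C. sentence makes no sense as printed, since it supplies a tablet to someone who has one. Once the missing negative is supplied, it sits awkwardly beside the requirement, in both 2.5 and 2.2, that candidates already have a device. At stake is whether one group of candidates, those with no device, is eligible in B.C. The protocol should not leave that to the person screening.

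**Working it through.** No arithmetic applies: the point rests on no sample size, power or error rate, and correcting the wording changes no stated figure. The check sets the rules side by side.

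**Step 1: polarity of the exclusion.** The list in 2.5 is introduced as people who will be excluded, and its last item is the ability to use a tablet. Compare this with the rest of the protocol:
- 2.5, inclusion: a computer or tablet is required.
- 2.3: consent is taken on Qualtrics, with a Zoom meeting to go through the form.
- 2.9: all data are collected by Qualtrics link and all sessions are held on Zoom, in both arms.
- 2.16: training time and sessions in the treatment group come from tablet usage data.
- Appendix B: SMART is delivered by computer or tablet.

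All of these assume participants who can operate such a device. No other place in the protocol states the exclusion the right way round, so nothing in the document overrides the printed text.

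**Step 2: apply 2.5 to the candidate types**, taking all other criteria as met.

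| Candidate | Evident intent | 2.5 as written |
|---|---|---|
| Has a computer or tablet, can use a tablet | Eligible | Excluded |
| Has a computer or tablet, cannot use a tablet | Excluded | Eligible |

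Both rows come out reversed. The planned enrolment of 82 (41 per arm, section 2.10) is meant to come from the first row, so under the literal rule almost every intended enrolment would be an eligibility breach.

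**Step 3: the device rules**, reading the B.C. sentence with *not* restored.

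| Candidate | Inclusion in 2.5 | Own-device screening in 2.2 | Tablet supply in 2.2 |
|---|---|---|---|
| Computer but no tablet, B.C. | Met | Met | May receive one; no conflict |
| Computer but no tablet, Ontario | Met | Met | None supplied; no conflict |
| Neither device, B.C. | Not met | Not met | May receive one; **effect on eligibility not stated** |
| Neither device, Ontario | Not met | Not met | None supplied; consistently ineligible |

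Only the third row is unresolved. The protocol gives no count of such candidates and describes the supply of tablets as rare.

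**The case against.** The strongest reply is that nobody would apply the exclusion as printed. The example about typing with the hands shows that a functional limitation was meant, the neighbouring inclusion criterion requires a device, and the whole trial runs online. Section 2.12 also has volunteers screened by telephone when they contact the research coordinator, which makes divergent literal readings across sites less likely. All of this stands, and it limits the practical consequence. It does not make the printed criterion correct.

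On devices, the reply is that 2.5 accepts a computer *or* a tablet, so the B.C. supply may simply help an enrolled participant who has a computer but no tablet. That also stands, and it confines the problem to candidates with neither device. The difference between the provinces is openly stated as a limit on supply and is not itself a contradiction.

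A reader might be tempted to go further in three ways, none of which the protocol supports:
- **That the trial will lose its target population.** This follows from the literal words only. The intent is evident and staff would probably screen accordingly.
- **That the group needing a tablet is large**, from the 86% (age 45-64) and 55% (over 65) in section 1.3. Those figures describe home internet access in B.C., not device ownership. Internet access is a separate inclusion criterion, and nothing says a supplied tablet would meet it.
- **That the RE-AIM reach denominator is inconsistent between provinces.** Section 2.8 glosses reach only as the target population and defines no denominator, so no inconsistency can be read from it.

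**Conclusion.** The point holds as a drafting error in an operative eligibility rule, together with a narrow ambiguity about devices.

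- **Exclusion criterion:** the error is certain on the text. Its size on paper is almost every intended enrolment; its likely effect on who is actually enrolled is small, assuming that screening follows the evident intent.
- **Device rule:** the ambiguity rests on reading the B.C. sentence with *not* restored, which is the only reading that makes sense of it. It affects only B.C. candidates who have neither a computer nor a tablet. Their number is not given and cannot be derived from the protocol.

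Neither part touches the randomised comparison, the sample size or the power. It is worth correcting because eligibility text should give the right answer when followed word for word, and the correction is cheap.

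**What to change.** 1. In 2.5, change the last exclusion from an ability to *an inability to use a tablet*.
2. In 2.2, restore the missing word so that the B.C. sentence refers to a participant who does *not* have a tablet.
3. Reconcile 2.2 with 2.5 by stating whether a supplied tablet satisfies the device inclusion criterion. If it does, say that this applies in B.C. only, since none are supplied in Ontario. If it does not, say that the supply is for participants who already qualify through a computer. The choice is the sponsor's; the protocol as it stands does not settle it.

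The cost is a few words in an amendment, with any screening form built from the printed text checked against it. No analysis, sample size or data collection needs to change.
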